# **CHAPTER 2: LITERATURE REVIEW**

## **2.1 Cardiovascular Diseases (CVD)**

Cardiovascular Diseases (CVD) affect the heart and blood vessels, leading predominantly to coronary artery disease, stroke, and peripheral arterial disease. They have assumed public health significance globally(Liu, 2014). In 2011, the United Nations (UN) formally recognized non-communicable diseases, including CVDs, as a major concern for global health and set out an ambitious plan to dramatically reduce their adverse effects in all regions. The sixth World Health Assembly in 2013 and the Sustainable Development Goals provided guidance for UN member states to achieve a one-third reduction in premature mortality due to these diseases by 2030(Alwan et al., 2011; United Nations, 2021).

## **2.2 Epidemiology of CVDs**

The Global Burden of Diseases estimates report (2019) showed that the number of persons living with CVDs almost doubled from 270 million in 1990 to 523.2 million in 2019 globally. An estimated 18.6 million CVD-related deaths occurred in 2019, contributing to about a third (32.8%) of all deaths globally and leading to a total of 393 million disability-adjusted life years lost. Over 85% of these CVD-related deaths resulted from ischemic heart disease and stroke, two diseases that maintained their lead as the major causes of death globally since 2000(NCD Allicance, 2019; Schettler & Brisse, 2017; WHO, 2019).

More than three-quarters of the CVD-related deaths took place in low- and middle-income countries, and out of the 17 million premature deaths (under the age of 70) due to non-communicable diseases in 2019, 82% occurred in these countries, with 37% caused by CVDs(World Health Organization, 2020). Whilst the CVD caseload doubled globally from 1990 to 2019, the number of persons living with these conditions almost tripled over the same period in Ghana. The Institute for Health Metrics and Evaluation estimated that CVDs contributed to 19% of all deaths in the country in 2019, and this proportion has also seen a sturdy rise since 2000(IHME, 2019).

## **2.3 Importance of CVDs**

#### **Economic Importance**

In addition to the staggering toll they take on human lives and health, CVDs wreak great havoc on countries' economies. They contributed to 55% of direct health costs and a 45% reduction in productivity globally in 2018(World Heart Federation, 2019). In the United States, CVDs were the most costly diseases with a price tag of $555 billion in 2016. Their economic burden is projected to worsen and be in trillions of dollars by 2035(RTI International, 2016). A systematic review by Gheorghe and colleagues on the economic burden of CVDs in Lower-Middle Income Countries(LMIC) suggested that the average costs per episode for hypertension and other generic CVDs ranged between $500 and $1500, whilst that for coronary heart disease (CHD) and stroke were in excess of $5000 per episode. They found the average monthly cost for hypertension treatment to be $22 whilst that for stroke and CHD ranged between $300 and $1000. In Summary they noted that these costs exceeded the total health expenditure per capita in most LMICs(Gheorghe et al., 2018). By 2030 the total global cost of CVD is set to rise from approximately US$863 billion in 2010 to a staggering US$1,044 billion(World Heart Federation, 2019).

#### **Comorbid effect of CVDs on COVID-19.**

The ongoing COVID -19 pandemic, caused by infection with the Severe Acute Respiratory Syndrome Coronavirus 2 (SARS-CoV-2), has further shown the clinical importance of CVDs (Chung et al., 2021). Over 40% of confirmed COVID-19 patients that required hospitalization reportedly had a history of cardiovascular diseases and their risk factors(Bax et al., 2020; Nishiga et al., 2020; Ogah et al., 2021; S. Shi et al., 2020). Several authors observed that a large proportion of deaths from infected patients could be attributed to cardiovascular diseases, including acute myocardial infarction, arrhythmias and heart failure(Bansal, 2020; Chatterjee & Cheng, 2020; Yi et al., 2021). A meta-analysis by Bae reported patients with CVDs to have a higher risk of developing the severe disease (44.4% vs 23.3%, OR 3.15, 95% CI 2.34 to 4.25) and death (35.7% vs 17.6%, OR 3.23, 95% CI 2.28 to 4.57) than those without CVDs(Bae et al., 2021). CVDs, therefore, amplified the lethal effect of the virus.

## **2.4 Hypertension**

Hypertension, defined as persistently high blood pressure (systolic BP ≥140 mmHg or the diastolic BP ≥90 mmHg or both), is the leading modifiable risk factor for CVD-related disability and mortality globally. In 2019, it was estimated to have accounted for 10.8 million deaths (19.2% of total deaths) and 235 million disability-adjusted life years globally (9.3% of total disability-adjusted life years)(Abbafati et al., 2020; Mills et al., 2020).

A meta-analysis by Lewington and colleagues found a doubling of the risk of ischemic heart disease and stroke with every 20 mmHg and 10 mmHg increase in SBP and DBP, respectively, starting from as low as 115 mmHg for SBP and 75 mmHg for DBP(Lewington et al., 2002). An Asian Pacific Cohort Studies Collaboration found similar associations, with each 10 mmHg increase in SBP found to be associated with a 45% higher risk of ischemic heart disease and about a 65% higher risk of ischemic or hemorrhagic stroke in those aged 55–64 years(Singh et al., 2013) Blood pressure rises with age and is higher in obese and overweight individuals (Kotchen, 2011). However, the onset of hypertension predates adulthood(Sekyere & Abena, 2018).

### **2.4.1 Adolescent hypertension**

Although thought to be an adult disease, arterial hypertension is established early in life. Early-onset hypertension is a predictor of adult hypertension and increases the risk of cardiovascular morbidity and mortality in adulthood(Oh & Hong, 2019). Studies have demonstrated that children with a single BP measurement >90th percentile are 2.4 times more likely to have an adult BP >90th percentile, and preventing pediatric elevated BP could eliminate 10% of adult elevated BP(Bao et al., 1995a; Kelly et al., 2015; Lauer et al., 1993). These and other findings have led to a paradigm shift from primary adult prevention to primordial prevention of hypertension in childhood(De Jesus, 2011b; Lloyd-Jones et al., 2010). Early recognition and management of children at high risk and those with hypertension are essential to decrease the substantial adult CVD burden(Flynn et al., 2017).

Song and colleagues reported a global pooled prevalence rates of 4.0% (95% confidence interval [CI]: 3.3%-4.8%) for hypertension and 9.7% (95% CI: 7.3%-12.4%) for prehypertension among persons 10-17 years(Song et al., 2019). Data from a population of over 54,000 children and adolescents aged 2-19 years across Africa gave a pooled prevalence of 5.5% (95% CI: 4.2-6.9) for elevated blood pressure (systolic or diastolic blood pressure ≥ 95^th^ percentile) and 12.7% (95% CI: 2.1-30.4) for slightly elevated blood pressure (systolic or diastolic blood pressure ≥ 90^th^ percentile and < 95^th^ percentile)(Noubiap et al., 2017). About 9.1% of adolescents in the Ashanti Region of Ghana were also found hypertensive (Sekyere & Abena, 2018). In all populations, the prevalence of elevated blood pressure was strongly associated with body mass index (BMI), being six times higher in obese children compared to those with normal weight(30.8% vs 5.5%; p<0.0001)(Noubiap, 2020).

### **2.4.2 Effect of uncontrolled hypertension in children and adolescents**

Hypertension in children is increasingly recognized as a serious public health problem, not only because of its rising prevalence with obesity but the growing evidence that elevated blood pressure early in life has detrimental lifelong cardiovascular effects(Bao et al., 1995b; Falkner & Lurbe, 2020; Theodore et al., 2015). In a recent systematic review and meta-analysis, elevated blood pressure in childhood or adolescence was significantly associated, in adulthood, with indicators of end-organ damage such as high pulse wave velocity or arterial stiffness (pooled odds ratio [OR] 1.83, 95% CI: 1.39-2.40), high carotid intima-media thickness (OR 1.60, 95% CI: 1.29-2.00) and left ventricular hypertrophy (OR 1.40, 95% CI: 1.20-1.64)(Yang et al., 2020). In youth, elevated blood pressure was also linked with cardiovascular disease and mortality in adulthood(Yang et al., 2020). After 20 years of following up a cohort of 8,720 adolescents found hypertensive during a medical examination, they were observed to have a relatively higher mortality risk due to CVD compared to the normotensive adolescents( Hazard ratio=1.5), with an exceptionally high risk for stroke mortality(Hazard ratio= 3.0)(Leiba et al., 2015).

Hypertension at any age is therefore associated with adverse cardiovascular outcomes, supporting the call by the World Health Assembly in 2013 for a 25% decrease in the prevalence of raised BP from its 2010 level by 2025 through risk factor reduction(Zhou et al., 2021). In addition to poor dietary and physical activity behaviours, smoking and alcohol abuse, one emerging risk factor for the development of hypertension is infection with the Human Immunodeficiency Virus (HIV) (Benzekri et al., 2018; Kwarisiima et al., 2016).

## 2**.5 HIV Cardiovascular disease and hypertension**

### **2.5.1 The Human Immunodeficiency Virus (HIV) Infection**

According to the World Health Organization, approximately 37.7 million people were living with HIV globally as of December 2020, over two-thirds of whom were in the WHO African Region and about 346,000 in Ghana(Ghana AIDS Commission, 2021a; WHO, 2021b). Adolescents and young persons form a growing proportion of people living with HIV(PLHIV) worldwide, and a focus on them is required to end AIDS and its sequelae as public health threats(UNICEF, 2020). In 2020, 1,750,000 adolescents were estimated to be living with HIV globally, with 150,000 of them being newly infected. The majority were in sub-Saharan Africa and about 23,000 in Ghana(Ghana AIDS Commission, 2021b; UNAIDS, 2021b).

Although there is no cure for HIV, increasing access to antiretroviral therapy, including treatment for opportunistic infections, has transformed the infection into a chronic disease. As a consequence, it is estimated that by 2030, the median age of PLHIV would increase from 43∙9 years in 2010 to 56∙5 years in 2030, by which time, 78% of them would have age-associated CVDs (Hsue & Waters, 2018; Smit et al., 2015).

### **2.5.2 HIV and CVDs**

Recent evidence has shown a relatively higher incidence of CVDs and CVD-related deaths among PLHIV than uninfected persons. A review by Alonso and colleagues reported that compared to uninfected persons, HIV positive persons had a higher incidence(per 1000 person-years) of CVD-related admissions( 10.8 vs 5.9), myocardial infarction( 1.4 vs 1.1), heart failure( 3.5 vs 1.1), stroke( 1.4 vs 0.5) and atrial fibrillation( 3.5 vs 2.9)(Alonso et al., 2019). Contributing to this is the relatively higher prevalence of CVD risk factors, particularly hypertension, amongst them. Appiah and colleagues, in a survey in Ghana, found a higher prevalence of hypertension ( 29% vs 15%), dyslipidemia(9% vs 5%) and diabetes(5% vs 0.6%) among persons living with HIV, compared to uninfected volunteers(Appiah et al., 2019).

### **2.5.3 HIV and hypertension.**

Hypertension is an emerging challenge among persons living with HIV (PLHIV). (Fahme et al., 2018; Peck et al., 2014; Xu et al., 2017). HIV-infected adults on treatment have a higher hypertension prevalence than uninfected individuals(Peck et al., 2014). A global meta-analysis suggests that 35% of all HIV-infected adults on ART have hypertension, compared with an estimated 30% of HIV-uninfected adults(Xu et al., 2017). More than half of ART-experienced individuals over 50 years are estimated to have hypertension(Fahme et al., 2018; Mbuthia et al., 2021; Pierre et al., 2019).

#### **Pathophysiology**

[figure not shown]

Figure 1Schematic representation of HIV-related mechanisms of hypertension(Fahme et al., 2018)

**Schematic representation of HIV-related mechanisms of hypertension(Fahme et al., 2018)**

Although older age, obesity, male gender family history of hypertension and level of physical activity play a role in the genesis of hypertension amongst PLHIV (Fiseha et al., 2019), contributing to their higher incidence and prevalence are the effects of ARV- and HIV-associated microbial translocation, chronic inflammation, immune reconstitution, dyslipidemia, renal disease and neuroendocrine response. These, directly and indirectly, lead to endothelial dysfunction, accelerated vascular ageing and arterial stiffness(figure 1) (Fahme et al., 2018). With a reported incidence (per 1000) of 10- 16 per month after ART initiation, the duration of HIV infection and treatment plays a significant role in the development of hypertension, putting perinatally- and behaviorally- infected adolescents at higher risk (Mulugeta et al., 2021; Rodríguez-Arbolí et al., 2017).

### **2.5.4 Adolescents living with HIV and hypertension.**

Like adults, HIV positive adolescents are at a relatively higher risk of hypertension than their uninfected age and sex-matched peers. Among adolescents living with HIV(ADLHIV) in Lagos, Adeloye et al. had a hypertension prevalence of 10.5%, with older age [odds ratio (OR) 1.557, 95% confidence interval (CI) 0.344–7.040], waist circumference (OR 6.435, 95% CI 1.396–29.666), duration on ART more than eight years (OR 1.308, 95% CI 0.332–5.153), and dyslipidemia (OR 2.942, 95% CI 0.726–11.914) predicting the risk of hypertension among them. (Adeloye et al., 2015). Ryscavage and colleagues found that perinatally infected adolescents have higher odds (3.4 (95% CI 1.48–7.66)) of developing hypertension than HIV-uninfected peers. After controlling for sex, race, and family history of hypertension, they still had 4.7 times the odds of being hypertensive(Ryscavage et al., 2019). These and other findings contributed to recommendations by the Expert Panel on Integrated Guidelines for Cardiovascular Health and Risk Reduction in Children and Adolescents to classify HIV infected children and adolescents as being at moderate risk of CVD, especially hypertension and calling for increased surveillance among them(De Jesus, 2011b).

To guide and standardize the surveillance for hypertension among children and adolescents, several clinical practice guidelines have been developed for service providers.

## **2.6 Clinical Practice Guidelines**

Field and Lohr have described clinical practice guidelines (CPG) as "systematically developed statements to assist practitioner decisions about appropriate health care for specific clinical circumstances" (Field & Lohr, 1990). Guidelines enhance patient care quality and promote patient safety through evidence-based practice(Dahm et al., 2009; Harrison et al., 2010; Horvath et al., 2010). They are also used to standardize clinical interventions for which health professionals may be held accountable(G. P. Browman, 2000; George P. Browman, 2005; Carlsen et al., 2007; Carlsen & Norheim, 2008).

### **2.6.1 Guidelines for screening and management of hypertension among children and adolescents.**

To help identify, prevent and appropriately manage hypertension in children and adolescents, several guidelines have been developed and updated, with adaptations done by various countries and professional bodies. The most commonly referenced is the Fourth Report by the National High Blood Pressure Education Program (NHBPEP) Working Group on Children and Adolescents(Falkner & Daniels, 2004). The report provides specific consensus and evidence-based statements on screening, diagnosis, investigation and management of hypertension among children and adolescents.

### **2.6.2 Screening for hypertension**

The guideline recommends annual screening for children and adolescents, beginning at three (3) years. However, more frequent screening was recommended for those with specific hypertension risks such as obesity, diabetes, renal disease, and those on treatment with drugs known to increase blood pressure(such as antiretroviral)(Saini et al., 2021).

### **2.6.3 Diagnosis of hypertension**

The guideline defined hypertension in children and adolescents as systolic BP (SBP) or diastolic BP (DBP) or both SBP and DBP, which is, on repeated measurement, at or above the 95th percentile for age, sex and height. BP between the 90th and 95th percentile in childhood was designated "prehypertensive".

It further recommended that

1. “BP should be measured in the right arm with an appropriate cuff size(Flynn et al., 2017).
2. Appropriate steps should be taken to ensure the child is comfortable and still for at least 5 minutes prior to measurement.
3. Home BP measurements may help monitor hypertensives but not diagnose new cases.
4. Although measurement with an automatic BP cuff (oscillation device) may be used to screen for elevated BP in the primary care setting, it should be repeated with auscultation if the BP reading is elevated.
5. If an auscultated BP measurement is elevated despite correct measurement technique, it should be repeated two more times at the same visit and the average of the last two auscultatory readings used as a final BP. The degree of elevation should be assessed based on this average with reference to normative BP values for age, sex and height and the revised hypertensive categories as outlined in Figure 2A (Flynn et al., 2017).
6. A diagnosis of paediatric hypertension can be made if the BP remains at or above stage 1 hypertension on three separate clinic visits (Flynn et al., 2017). The timeline for these follow-up BP assessments is as outlined in figure 2A.
7. Compared to adults, their report gave no strict BP cut-off for a hypertensive crisis in children. However, it stated that severe hypertension warranting assessment in the emergency department depends on clinical symptoms, including irritability, headache, oedema, visual changes, or severe abdominal pain(Chandar & Zilleruelo, 2012; N. H. Patel et al., 2012; Stein & Ferguson, 2016).
8. Due to its superiority over isolated BP measurement in diagnosing hypertension and its ability to identify some secondary causes of hypertension, ambulatory blood pressure monitoring (ABPM) was recommended for screening or in confirming the diagnosis of hypertension if
   1. BP remains in the elevated BP category for ≥1 year
   2. BP remains in stage 1 hypertension category over three successive visits.
   3. The patient has high-risk conditions for hypertension (i.e., CKD, diabetes, obesity, or prematurity)
   4. Whitecoat hypertension is suspected”.

[figure not shown]

**Figure 2** (A) Blood pressure (BP) categories definitions and management algorithm (B) Minimum systolic and diastolic BP that warrants further investigation for girls and boys based on age(Flynn et al., 2017)

### **2.6.4 Investigating the aetiology of hypertension**

Because children and adolescents have a higher prevalence of secondary hypertension than the adult population (Falkner & Daniels, 2004), the guideline recommends a thorough screen for causative factors once a diagnosis of hypertension is made. This assessment should include a thorough perinatal, nutritional, physical activity, psychosocial, medical and family history. It should be followed by a complete physical examination to help provide clues to potential secondary causes of hypertension and to assess possible end-organ damage. It should include assessing the BMI, checking BP in multiple limbs to diagnose coarctation of the aorta, and other assessments based on the clinical history. To detect underlying secondary causes, laboratory evaluation of newly diagnosed children is recommended. Assessments for renal, endocrine and other conditions suggested by history and physical examination is also recommended. Clinicians are encouraged to screen for conditions that are likely to increase stress, including depression, anxiety, trauma, or bullying(Flynn et al., 2017). Additional recommended assessments include those for target organ damage. These include assessments for

1. “Central arterial stiffness using pulse wave velocity, cardio-ankle vascular index, carotid intima-media thickness and flow-mediated dilatation.
2. left ventricular hypertrophy using electrocardiogram or echocardiography
3. Renal and renovascular disease using renal ultrasound or CT scan, microalbuminuria and other biochemical tests, including serum uric acid.” (Flynn et al., 2017)

Beginning with the history, topics that should be addressed include the child's perinatal course, diet, exercise, obesity, medications, and family history. Social history warrants particular attention as family income, parental education, poor sleep, and a lack of physical activity are independent risk factors for increased BP among children and adolescents (Y. Shi et al., 2012).

A comprehensive physical examination should then be performed, covering each system involved in any differential diagnosis considered. Electrolytes, creatinine, lipid profile, blood urea nitrogen, and urinalysis are to be done for all children and adolescents with hypertension(Flynn et al., 2017).

### **2.6.5 First-line management of hypertension**

To prevent long-term sequelae of paediatric and adolescent hypertension and reverse end-organ damage, the guideline recommends a systematic approach to hypertension management once a diagnosis is made(see figure 1 A) (Flynn et al., 2017). The goals for management include targets for systolic and diastolic BPs.

In all cases, the first step in management involves lifestyle modifications, such as age-appropriate exercise and diet modifications(Flynn et al., 2017). For those within the category of elevated BP, lifestyle modifications should be implemented for approximately six months, after which the BP should be reassessed. Recommended target for BMI during this period is to have it <85^th^ percentile (Nerenberg et al., 2018). The indications for initiating pharmacotherapy include failure of lifestyle modifications, symptomatic hypertension, evidence of target organ damage, comorbid diabetes or chronic kidney disease, or stage 2 hypertension at presentation(Nerenberg et al., 2018; Y. Shi et al., 2012).

Lifestyle modifications should then continue to be used alongside pharmacotherapy, and regular follow-up appointments are recommended to monitor the BP until it is within target.

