### **2.6.7 Referral**

Referral to a subspecialist should be considered for hypertension that does not respond to 6 months of lifestyle modifications, monotherapy-resistant, secondary or stage 2 hypertension, and symptomatic forms of hypertension. In remote areas where there might not be access to a paediatric nephrologist, clinicians are advised to consider telephone or telehealth consultation with a specialist. If urgent or emergent, transfer to the nearest centre with paediatric subspecialty care may be warranted(Saini et al., 2021).

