### **3.3.9 Outcomes**

#### **a. Primary outcomes**

The primary outcome will be the effect of the intervention on healthcare workers’ adherence to the guideline. It will assess adherence to recommendations on the

1. frequency of screening
2. Detection of elevated or high BP,
3. Investigation of high BP and
4. Management of elevated or high BP.

These will be assessed using a data extraction tool based on the HIV client care booklet. The tool will extract the data from the client care records of adolescents who received care within the period of interest. At baseline, it will assess the records of 20 randomly selected adolescents who received care at the facility six months prior to the assessment and extract the data from their most recent visit. At follow up, data will be extracted from the most recent visit of 20 randomly selected adolescents who received care at the facility after the intervention commenced.

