**DATA EXTRACTION FORM**

| **Name of reviewer:……………………………………. Date:………………….** | | | |
| --- | --- | --- | --- |
| **Demographic characteristics** | | | |
| **Question No.** | **Variable** | **Variable code** | **Values** |
| 1) | Folder ID | FID | ………………….. |
| 2) | Study ID | SID | …………………. |
| 3) | District/Municipality | AREA | ………………….. |
| 4) | Facility | FAC | ………………….. |
| 5) | Date of data collection | DATE | dd-mm-yyyy………………………. |
| 6) | Sex | SEX | 0-Female  1-Male |
| 7) | Age (years) | AGE | ……………………………. |
|  |  |  |  |
| 8) | Occupation | OCC | ………………………………. |
| 9) | Highest educational level | EDUC | 1-No formal education  2-Primary school  3-High school  4-Tertiary |
| 10) | Marital status | MSTAT | 1-Single  2-Married  3-co-habitting |
| 11) | Religion | REL | 1-Christian  2-Muslim  3-Other (specify) |
| **Section II – Clinical characteristics** | | | |
| **12** | Date of HIV diagnosis | DD_HIV | dd-mm-yyyy………………………. |
| **13** | Age at HIV diagnosis | **AD_HIV** | ………………….years |
| **14** | HIV Type |  | 1-I 2-II 3-I & II |
| 15 | Weight at baseline | WT_BASE | ……………………………(Kg) |
| 16 | Weight at end line | WT_END | ……………………………(Kg) |
| 17 | Height | HT | ……… (m) |
| 18 | Date of ART initiation | DAI | dd-mm-yyyy………………………. |
| 19 | Age at ART initiation | AAI | …………………………………. |
| 20 | WHO Stage at ART initiation | WSI | 1-1  2-2  3-3  4-4 |
| 21 | Current ART regimen | CAR | ----------------- |
| 21 | Previous ART Regimen | PAR | ……………………….    ………………………. |
| 22 | Viral load at baseline | VL_B | 1-Suppressed  2-Unsuppressed  3-None |
| 23 | Viral load at baseline | VL_B | 1-Suppressed  2-Unsuppressed  3-None |
| 24 | Systolic BP at last visit | SBP | 1………..  2.Not recorded |
| 25 | Diastolic BP at last visit | DBP | 1………..  2.Not recorded |
| 26 | Action taken on BP | BP_ACT | 1. None  2. Rechecked to confirm  3. Given appointment to recheck  4. Counselled on lifestyle  5. Referred |
| 26 | Smoking | SMK | Yes___ No___ Ex____  If Yes: Type___________  Number /day or week_______ |
| 28 | Alcohol use | ALC | Yes___ No___  If Yes (Check one):  Every day___ ≥ Once weekly ___ ≥ Once monthly___ |

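### The extraction form has no code or field for antihypertensive medicine, so the management component of the primary outcome cannot capture drug treatment

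*Protocol*

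**What the plan says.** Protocol section 3.3.9a defines the primary outcome as adherence to the guideline in four respects, the fourth being "Management of elevated or high BP". It names the instrument for all four: "These will be assessed using a data extraction tool based on the HIV client care booklet". Only one visit per adolescent is read; at follow-up, "data will be extracted from the most recent visit of 20 randomly selected adolescents who received care at the facility after the intervention commenced".

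Section 2.6.5 sets out the guideline's management step. It begins with lifestyle measures: "In all cases, the first step in management involves lifestyle modifications". It then lists when medicine is started: "The indications for initiating pharmacotherapy include failure of lifestyle modifications, symptomatic hypertension, evidence of target organ damage, comorbid diabetes or chronic kidney disease", and stage 2 hypertension at presentation. The two go together: "Lifestyle modifications should then continue to be used alongside pharmacotherapy". Section 2.6.7 adds: "Referral to a subspecialist should be considered for hypertension that does not respond to 6 months of lifestyle modifications", and names further groups for referral.

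The Data Extraction Form, Section II, has one item for what was done about the reading, "Action taken on BP" (BP_ACT). Its codes run from 1 to 5: no action, recheck to confirm, appointment for a recheck, lifestyle counselling, referral. There is no code for medicine, no 'other' option and no instruction on whether several codes may be marked. The only medication fields are the current and previous ART regimens.

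**The concern.** A component of the primary outcome includes, by the protocol's own account of the guideline, an action that its only named instrument cannot record. The interview content listed in section 3.3.9b does not ask about antihypertensive medicine, and it serves the secondary outcomes. Section 3.3.3 does not exclude adolescents already on such medicine, so their records can be drawn.

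This cannot be left to a statistical analysis plan. A plan can decide how codes become a score, but it cannot recover a variable that was never abstracted. The BP_ACT list is also an unbroken run from 1 to 5, so a category lost in text conversion is unlikely.

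At stake is whether the management result means what its name says. A visit managed by medicine alone can look the same as a visit where nothing was done. A visit with counselling and medicine looks the same as one with counselling only.

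**Working it through.** **1. The plan's own figure.** The protocol gives no figure for the management component. Its sample size (section 3.3.5) concerns BP screening: 17% against 34%, two-sided 5%, 80% power, 20 adolescents per facility, ICC 0.05. It reproduces:

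- 103 per arm without clustering
- design effect 1 + 19 × 0.05 = 1.95
- 103 × 1.95 = 200.85, and 200.85 / 20 = 10.04 facilities per arm
- ten facilities per arm give 80.2% power, so the stated 10 stands

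A missing action code does not change this calculation.

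**2. Guideline step against form code.**

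| Action in sections 2.6.3, 2.6.5 and 2.6.7 | BP_ACT code |
|---|---|
| Repeat the measurement | 2 |
| Follow-up appointment | 3 |
| Lifestyle measures | 4 |
| Referral | 5 |
| Antihypertensive medicine started, continued or changed | none |

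**3. What happens to a drug-treated visit.** There are two cases. If the record shows medicine and nothing else, code 1 or a blank is all that remains. If it also shows a recheck, an appointment, counselling or referral, one of codes 2 to 5 applies and the medicine is not seen. No text in the protocol says which code to use.

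**4. How many records the component rests on.** Inputs: 12 facilities × 20 adolescents = 240 records per arm (sections 3.3.5 and 3.3.6); 17% and 34% of visits with a BP (section 3.3.5); 10.5% hypertensive among adolescents living with HIV in one Lagos sample (section 2.5.4). Assumption: whether BP is taken does not depend on BP status.

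- Control: 240 × 0.17 × 0.105 = 4.3
- Intervention: 240 × 0.34 × 0.105 = 8.6

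The component also covers elevated BP. Adding the 12.7% with slightly elevated BP pooled across African youth (section 2.4.1, a general population used here as an assumption) gives 0.105 + 0.127 = 0.232:

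- Control: 240 × 0.17 × 0.232 = 9.5
- Intervention: 240 × 0.34 × 0.232 = 18.9

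**5. Weight of one misread record.**

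| Denominator | Control | Intervention |
|---|---|---|
| Hypertensive readings only | 1/4.3 = 23 points | 1/8.6 = 12 points |
| Elevated or hypertensive readings | 1/9.5 = 11 points | 1/18.9 = 5 points |

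These are points per misread record, not an estimate of total error, because the protocol gives no share treated with medicine.

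**6. Direction.** Let *m* be the true share of high readings with any management action and *d* the share managed by medicine alone. If the latter are all read as no action, each arm shows *m* − *d*. The between-arm difference then shifts by −(*d* in intervention − *d* in control). With equal *d* the shift is zero, whatever the number of high readings found. The protocol gives neither value of *d*.

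**The case against.** The strongest reply is that a drug start following section 2.6.5 would seldom stand alone. Lifestyle measures come first and continue with medicine, follow-up appointments are recommended, and section 2.6.7 has referral considered for three of the drug indications (lifestyle failure, symptoms, stage 2). Such visits would usually earn code 3, 4 or 5. This stands, and it rules out a stronger reading that a reader might infer: that every adolescent managed with medicine is scored as no action, so that guideline-concordant care counts as non-adherence. No passage sets that rule. The no-action code or a blank is forced only when medicine is the sole recorded action.

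A reader might also infer that the gap dilutes the intervention effect because intervention facilities find more high readings. Step 6 shows that this does not follow. It needs a larger medicine-only share in the intervention arm, or all records as denominator, and the protocol states neither.

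Nor does an adolescent controlled on medicine count as a failure of management. With a normal reading, that record falls outside a component about elevated or high BP on its natural reading. The form merely cannot tell such an adolescent from an untreated one with normal BP.

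Drug starts may be few: diagnosis needs three visits (section 2.6.3), elevated BP has about six months of lifestyle measures first, and follow-up is six months. That is fair, but several listed indications do not wait for lifestyle failure, and adolescents already on treatment are not excluded.

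Finally, section 2.6.5 is literature review, and section 3.3.9a does not say which guideline text scores adherence. The fix should therefore refer to the adopted text. The form's lack of any field for investigating high BP is a separate gap in the same instrument.

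**Conclusion.** The concern holds as a gap in measurement. The form cannot record antihypertensive treatment, so the management component cannot capture it. Management by medicine alone can be misread as no action, and medicine given with another action is invisible.

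The total size is unknown because the drug-treated share is not given, and no direction of between-arm bias can be claimed. What can be said is that the component rests on few records: about 4 control and 9 intervention hypertensive readings, or about 9 and 19 if elevated BP is added. One misread record then moves the proportion by roughly 5 to 23 points, depending on arm and denominator. These counts assume that the Lagos prevalence, the pooled African figure and the planning rates apply here, and that BP checking is unrelated to BP status. The sample size for screening is unaffected. The change is worth making because it is cheap before extraction and cannot be made good in the analysis.

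**What to change.** Before baseline extraction:

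- Add to BP_ACT a code for antihypertensive medicine started, continued or changed, and an 'other (specify)' option.
- Add a yes/no field for being on antihypertensive medicine at the extracted visit.
- State on the form that codes may be combined.
- Name the guideline text against which management is scored, and count the drug code as a management action where that text calls for it.
- Use the identical form in both arms and at baseline and follow-up.

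This concerns data capture only and sets no treatment rule. The cost is one code, one option and one field on the tablet form, read from the same client care booklet. If the change comes after baseline, up to 24 × 20 = 480 records would need a second abstraction for the rounds to be comparable.
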